## Abstract

**Background:**

Glucocorticoids are extensively utilized in clinical medicine, yet their therapeutic benefits are often accompanied by adverse effects, among which insomnia is particularly prevalent. This sleep disturbance not only compromises treatment efficacy but also significantly diminishes patients’ quality of life. Notably, no targeted therapeutic interventions are available that specifically address glucocorticoid-induced insomnia. Acupuncture therapy has potential as a promising complementary approach for managing sleep disorders in patients receiving glucocorticoid treatment.

**Methods:**

This study presents a randomized, sham-controlled clinical trial protocol. A total of 76 patients with glucocorticoid-induced insomnia will be randomly assigned to either the acupuncture group or the sham acupuncture group. The primary outcome is the change in Pittsburgh Sleep Quality Index total score from baseline to post-intervention. The key secondary outcomes are the changes from baseline to post-intervention in the Insomnia Severity Index score, polysomnography-derived total sleep time, and polysomnography-derived sleep efficiency. Other exploratory outcomes include additional polysomnographic parameters, actigraphy parameters, peripheral 5-hydroxytryptamine levels, emotional status, and daytime functioning.

**Discussion:**

This trial will evaluate the efficacy and safety of acupuncture for glucocorticoid-induced insomnia and explore potential physiological mechanisms in this specific patient population.

**Clinical trial registration:**

https://itmctr.ccebtcm.org.cn/mgt/search, identifier: ITMCTR2025000220.

## Introduction

1

Glucocorticoids (GCs) were first applied clinically by Hench et al. in 1950 for rheumatoid arthritis treatment, earning the Nobel Prize in Physiology or Medicine the following year (1). Despite their widespread clinical use for anti-inflammatory, immunosuppressive, and antipyretic effects, GCs exhibit numerous adverse effects (2, 3), including hypertension, diabetes mellitus, obesity, osteoporosis, and peptic ulcer exacerbation (potentially leading to hemorrhage or perforation) (4), and even cause neurological symptoms. Neuropsychiatric complications may manifest as personality changes, psychosis, or even epileptic seizures (5).

Among these, glucocorticoid-induced insomnia (GII)—characterized by excitation, agitation, anxiety, depression, or mania—represents the most prevalent complication (6). The clinical manifestations of GII include sleep initiation/maintenance difficulties, reduced sleep quality, and decreased total sleep time (TST), warranting clinical attention, as chronic insomnia may exacerbate pre-existing psychiatric symptoms and compromise GCs therapeutic outcomes (7).

To our knowledge, no randomized controlled trial has specifically targeted glucocorticoid-induced insomnia, and current management generally follows established protocols for primary insomnia. Conventional treatments for insomnia include pharmacotherapy (benzodiazepines, nonbenzodiazepine hypnotics, antidepressants, and antihistamines) and nonpharmacological interventions. While rapid-acting, pharmacological options carry risks of hangover effects, cognitive impairment, and dependence (8). Cognitive behavioral therapy for insomnia (CBT-I) and other psychotherapeutic approaches are generally accepted internationally as the primary recommended treatment for chronic insomnia disorder (9). However, due to their time-intensive nature and because physicians need much professional training to conduct them, these methods are not fully implemented in China. Other guideline-endorsed modalities (light therapy, physical therapy, and sleep hygiene education) demonstrate limited efficacy and stability, with the European Insomnia Guidelines rating evidence for light therapy and physical therapy as low quality (10).

Traditional Chinese Medicine (TCM) is effective for treating insomnia (11, 12), yet the literature reveals no clinical studies on TCM approaches for treating GII. Acupuncture is a branch of TCM and offers distinct advantages as a simple, accessible, and cost-effective intervention, with demonstrated improvements in sleep efficiency (SE), daytime functioning, mood regulation, and sleep architecture (13–15). Our prior randomized controlled trial (RCT) revealed that acupuncture has better clinical efficacy and safety for insomnia than sham acupuncture. It significantly improved sleep quality and daytime function, reduced insomnia severity, and adjusted mood in insomnia patients (16). Acupuncture for insomnia has a profound theoretical basis as well as an evidence base. However, the effects of acupuncture on GII remain unexplored. Therefore, this study is a RCT designed to explore the effect of acupuncture on the treatment of GII. It introduces a multidimensional evaluation scheme to comprehensively assess the specific efficacy and safety of acupuncture for GII.

In addition to the conventional subjective sleep assessment scale, polysomnography (PSG) and actigraphy (ACT) will be used in this study. The strategy of using PSG for screening enrolled patients and both PSG and ACT for monitoring sleep changes pre−/post-intervention offers distinct advantages. PSG remains the gold standard for detailed sleep architecture analysis, providing high-resolution data on sleep stages (e.g., rapid eye movement sleep, nonrapid eye movement sleep), respiratory events, and limb movements through multimodal recordings (17, 18). However, its laboratory setting and intrusive nature may alter natural sleep patterns. To solve this problem, we will use PSG data from the second night for analysis to reduce the “first-night effect” and will use ACT as a complementary indicator of objective sleep. ACT, although less precise in sleep staging, enables long-term, unobtrusive monitoring in real-world environments, capturing sleep–wake patterns over extended periods (19). Circadian rhythm disruption is likely one of the core mechanisms underlying GII (20). In addition, dysregulation of the hypothalamic–pituitary–adrenal (HPA) axis serves as a pivotal pathological mechanism in sleep disturbances. The rationale for monitoring serotonin 5-HT levels lies in its critical role in insomnia for the HPA axis. GCs disrupt the HPA axis and interact with serotonergic neurotransmission (21), which is pivotal in sleep–wake regulation (22). Modern mechanistic research suggests that GCs can cause hyperpolarization of nerve cell membranes, selectively inhibit spontaneous electrical activity, and enhance the activity of dopamine *β*-hydroxylase and phenylethanolamine N-transmethylase, increase the synthesis of norepinephrine and epinephrine, inhibit the activity of tryptophan hydroxylase, reduce the concentration of central 5-HT, and lead to mental abnormalities. This is an important mechanism for causing insomnia (23, 24). Although peripheral 5-HT is predominantly synthesized outside the central nervous system (e.g., in the gut and platelets), some evidence suggests that its levels may be influenced by central serotonergic activity via indirect pathways such as the vagus nerve and inflammatory signals (25). This study will include peripheral serum 5-HT as an exploratory biomarker to generate preliminary mechanistic insights into acupuncture treatment for GII.

Based on our literature search, no prior randomized controlled trial has specifically investigated the therapeutic efficacy of acupuncture for glucocorticoid-induced insomnia while incorporating comprehensive biomarker analysis. The present study employs a rigorous design to address this gap. Based on this framework, we proposed two testable hypotheses: (1) Acupuncture significantly improves both subjective sleep scales and objective sleep parameters compared with those of sham acupuncture in GII patients. (2) The clinical benefits of acupuncture correlate with measurable changes in peripheral 5-HT levels, suggesting that the modulation of serotonergic pathways is a potential mechanism for the therapeutic effects of acupuncture in GII patients.

## Methods/design

2

### Study design

2.1

This study is designed as a single-centre, sham-controlled, randomized controlled trial. This clinical trial will be conducted at the Acupuncture Department of the First Affiliated Hospital of Zhejiang Chinese Medical University. This trial was rigorously designed according to the Consolidated Standards of Reporting Trials (CONSORT) guidelines and the Standards for Reporting Interventions in Clinical Trials of Acupuncture (STRICTA) (Table 1). In addition, the study protocol strictly adheres to the Standard Protocol Items: Recommendations for Interventional Trials (SPIRIT) guidelines (See the supplementary material). The study flowchart and procedure are depicted in Figure 1 and Table 2.

**Table 1 tab1:** STRICTA of acupuncture treatment.

Item	Detail	Description
1. Acupuncture rationale	(1a) Style of acupuncture	Traditional Chinese Medicine
	(1b) Reasoning for treatment provided, based on historical context, literature sources, and/or consensus methods, with reference where appropriate	Textbook of the meridian, literature review of acupuncture for insomnia
	(1c) Extent to which treatment was varied	Formularized
2. Details of needling	(2a) Number of needle insertions per subject per session	4
	(2b) Names	HT7, KI7
	(2c) Depth of insertion, based on a specified unit of measurement, or on a particular tissue level	HT7: Vertical insertion, 0.3–0.5 cun; KI7: Vertical insertion, 0.5–1.0 cun
	(2d) Response sought	de qi
	(2e) Needle stimulation	manual
	(2f) Needle retention time	20 min
	(2g) Needle type	0.25 × 40 mm needles (Andi, Guizhou, China), stainless steel
3. Treatment regimen	(3a) Number of treatment sessions	10
	(3b) Frequency and duration of treatment sessions	Three sessions per week for the first 3 weeks and one session in the final (fourth) week, giving a total of 10 sessions.
4. Other components of treatment	(4a) Details of other interventions administered to the acupuncture group	none
	(4b) Setting and context of treatment, including instructions to practitioners, and information and explanations to patients	All interventions will be administered at a same clinical site by two licensed acupuncturists who will receive identical standardized training in the study protocol prior to trial initiation.
5. Practitioner background	(5) Description of participating acupuncturists (qualification or professional affiliation, years in acupuncture practice, other relevant experience)	Two licensed acupuncturists (minimum 3 years clinical experience).
6. Control or comparator interventions	(6a) Rationale for the control or comparator in the context of the research question, with sources that justify this choice	This method optimizes blinding integrity and participant expectancy while providing a credible placebo comparator with minimal physiological activity.
	(6b) Precise description of the control or comparator. If sham acupuncture or any other type of acupuncture-like control is used, provide details as for Items 1 to 3 above.	This study employs the Streitberger needle as the control intervention. See details in methods.

**Figure 1 fig1:**
[figure not shown]
Flow diagram. BAI, Beck Anxiety Inventory; BDI, Beck Depression Inventory; FSS, Fatigue Severity Scale; ESS, Epworth Sleepiness Scale; ISI, Insomnia Severity Index; PSG, Polysomnography; PSQI, Pittsburgh Sleep Quality Index; 5-HT, 5-Hydroxytryptamine.

**Table 2 tab2:** Trial processes chart.

Week	0	1	2	3	4	5, 8–9
	Baseline	Treatment phase				Follow-up phase
PATIENTS						
Telephone reservation	**×**					
Enrolment	**×**					
Sign informed consent	**×**					
Clinical interview	**×**					
Sleep scales	**×**					
Physical examination	**×**				**×**	
Laboratory test	**×**				**×**	
PSG	**×**				**×**	
GROUPS						
Acupuncture group		Ten treatments				
Sham- acupuncture group		Ten treatments				
OUTCOME MEASUREMENT						
PSQI	**×**				**×**	**×**
ISI	**×**				**×**	**×**
PSG	**×**				**×**	
ACT	**×**				**×**	
5-HT	**×**				**×**	
BAI	**×**				**×**	
BDI	**×**				**×**	
FSS	**×**				**×**	
ESS	**×**				**×**	
Sleep diary	**×**	**×**	**×**	**×**	**×**	
Success of subject-blinding test					**×**	
ADVERSE EVENTS						
Reasons for dropouts or withdrawals		**×**	**×**	**×**	**×**	**×**
Patient’s compliance					**×**	**×**

ACT, Actigraphy; BAI, Beck Anxiety Inventory; BDI, Beck Depression Inventory; ESS, Epworth Sleepiness Scale; FSS, Fatigue Severity Scale; ISI, Insomnia Severity Index; PSG, Polysomnography; PSQI, Pittsburgh Sleep Quality Index; 5-HT, 5-hydroxytryptamine.

### Participants and setting

2.2

We will recruit eligible participants who meet the operational definition of glucocorticoid-induced insomnia described below from the Acupuncture Department of the First Affiliated Hospital of Zhejiang Chinese Medical University. Subjects will be randomly assigned to 2 parallel groups based on randomization numbers: the acupuncture group and the sham acupuncture group, with an enrolment ratio of 1:1. Written informed consent will be obtained from all participants. This study was approved by the ethics committee of the First Affiliated Hospital of Zhejiang Chinese Medical University (no. 2024-KLS-089-02). This study will be conducted in accordance with the Declaration of Helsinki.

Operational definition of glucocorticoid-induced insomnia: In this trial, GII is operationally defined as insomnia meeting the applicable ICSD-3 diagnostic criteria (26) after documented systemic glucocorticoid exposure. Eligible patients must have either new-onset insomnia or a clear worsening of pre-existing mild sleep complaints that did not meet full ICSD-3 criteria before the index exposure, with full diagnostic criteria first met within 14 days after glucocorticoid initiation or clinically meaningful dose escalation, while receiving glucocorticoids at ≥5 mg/day prednisone equivalent. Patients who met full ICSD-3 criteria for insomnia before the index glucocorticoid exposure will not be eligible. The diagnosis will be based on a structured clinical interview, medical record review, a 1-week sleep diary, PSQI >5, ISI assessment, and baseline polysomnography showing objective total sleep time <6 h, consistent with recommended insomnia assessment procedures (27).

Glucocorticoid exposure will be recorded in detail, including drug type, route, daily prednisone-equivalent dose, administration time, start date, dose-escalation date, treatment duration, and dose stability. This information is collected because glucocorticoid-associated sleep disturbance has been reported in clinical and mechanistic studies and may be influenced by glucocorticoid dose, duration, and circadian timing (24, 28). Patients who met full ICSD-3 criteria for insomnia before the index glucocorticoid initiation or dose escalation, those with prior regular sedative-hypnotic use, and those with other primary sleep disorders will be excluded. Potential confounders, including underlying disease activity, pain, emotional status, caffeine or alcohol use, and concomitant sleep-affecting medications, will be documented at baseline and follow-up. Unauthorized sedative-hypnotic use and major changes in glucocorticoid exposure or other sleep-affecting medications during the trial will be recorded. A major change in glucocorticoid exposure is predefined as either (1) a > 50% change in daily prednisone-equivalent dose relative to baseline or (2) initiation or cessation of systemic glucocorticoid therapy during the treatment phase. These events will be addressed in per-protocol and sensitivity analyses.

The study will span 8–9 weeks, comprising a screening phase, a treatment phase and a follow-up phase (1-week follow-up and 1-month follow-up). The 1-week follow-up was selected to capture the most direct and immediate effects following intervention completion, as 1 week is sufficient for participants to adopt and adapt to new sleep patterns. Compared with more frequent assessments (e.g., every few days), the 1-week interval imposes less burden on participants, thereby enhancing study retention and data quality. The 1-month follow-up was chosen because it represents a critical time point for evaluating whether therapeutic benefits are sustained after the intervention is withdrawn. From a clinical perspective, poor sleep persisting for more than 1 month is generally considered one of the important time thresholds for diagnosing insomnia (29); therefore, the 1-month assessment helps determine whether the intervention has truly modified the disease trajectory rather than merely providing transient relief.

#### Inclusion criteria

2.2.1

(1) Met the above diagnostic criteria for insomnia according to the ICSD-3 criteria;(2) Age 18–65 years, gender is not limited;(3) A total PSQI score >5;(4) Objective TST of <6 h through PSG;(5) Participants receiving systemic glucocorticoid therapy at a dose of ≥5 mg/day prednisone equivalent, with either new-onset insomnia or a clear worsening of pre-existing mild sleep complaints that did not meet full ICSD-3 criteria before the index exposure, and with full diagnostic criteria first met within 14 days after glucocorticoid initiation or dose escalation. Glucocorticoid type, route, daily prednisone-equivalent dose, administration time, start date or dose-escalation date, and planned dose adjustment will be recorded.(6) No sedative-hypnotic medications were taken prior to participation in this study;(7) No acupuncture interventions were administered during the 6-month period prior to the study;(8) Voluntarily provided written informed consent.

#### Exclusion criteria

2.2.2

(1) Those with severe cardiac, hepatic or renal functional impairment and respiratory, haematologic or psychiatric system diseases;(2) Patients who met full ICSD-3 diagnostic criteria for insomnia before the index glucocorticoid initiation or dose escalation; mild pre-existing sleep complaints that did not meet full ICSD-3 criteria will not, by themselves, constitute an exclusion criterion;(3) Patients with unstable underlying disease, severe pain, acute infection, or other clinical conditions judged by investigators to be the primary cause of insomnia;(4) Patients who used sedative-hypnotics before participation, or who initiated or substantially changed other medications known to affect sleep within 2 weeks before screening, including antidepressants, antipsychotics, opioids, stimulants, or other centrally acting medications, unless the regimen for those other medications is stable and can be documented;(5) Lactating or pregnant women;(6) Patients with infectious diseases, such as those suffering from tuberculosis, hepatitis or acquired immune deficiency syndrome;(7) People who are not suitable for acupuncture treatment, such as those with unhealed trauma, severe skin diseases, allergies;(8) Sleep PSG showing a sleep apnoea-hypopnea index ≥10/h;(9) Sleep PSG showing periodic limb movements during sleep>15 times/h;

#### Withdrawal criteria

2.2.3

(1) Patients who were lost to contact during the treatment or follow-up phase;(2) Patients who refused to continue treatment during the treatment phase;(3) Those who discontinued treatment due to adverse events, which were recorded;(4) Patients whose disease progressed during the course of the study, making them unsuitable for continuation;(5) Patients who did not comply with the subject research process after entering the study;(6) Those who were difficult to assess due to poor adherence to and noncompliance with medical advice during the course of treatment;(7) Those who take sedative-hypnotic drugs without authorization in the course of treatment.

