#### Data sets definition

2.6.1

FAS: All randomized participants who received at least one intervention and had at least one post-baseline efficacy assessment. This set will be considered a modified intention-to-treat (ITT) principle. Participants who experience major changes in glucocorticoid exposure will be retained in the FAS.

PPS: Subjects who met inclusion/exclusion criteria, completed ≥80% of acupuncture sessions, and had no major protocol violations (e.g., unauthorized use of sedative-hypnotic medications). Participants who experience major changes in glucocorticoid exposure will be excluded from the per-protocol set.

Safety Set (SS): All subjects who received at least one intervention and had safety data recorded. Participants who experience major changes in glucocorticoid exposure will be retained in the SS.

Cases with unauthorized use of sedative-hypnotic medications will be excluded from the PPS but retained in the FAS and SS analyses.

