#### Primary and secondary analyses

2.6.2

All statistical tests will be two-sided, with *p* < 0.05 considered statistically significant for the primary outcome. The primary analysis will use a mixed model for repeated measures with PSQI total scores at all post-baseline visits (post-treatment, 1-week follow-up, and 1-month follow-up) as the dependent outcomes. Group, visit, and the group-by-visit interaction will be included as fixed effects, and baseline PSQI score will be entered solely as a covariate. Within-participant correlations will be modeled using an unstructured covariance matrix, and parameters will be estimated by restricted maximum likelihood. The adjusted between-group mean difference at the post-treatment visit, with its 95% confidence interval, is prespecified as the primary comparison; the 1-week and 1-month contrasts are secondary longitudinal comparisons.

For continuous secondary outcomes measured repeatedly, MMRM or generalized estimating equations will be used as appropriate to the outcome distribution and measurement schedule. The primary MMRM will use all available post-baseline observations under a missing-at-random assumption without single imputation. Multiple imputation will be used as a supportive sensitivity analysis, and a delta-adjusted pattern-mixture analysis will assess robustness to departures from the missing-at-random assumption. Major changes in glucocorticoid exposure will be treated as intercurrent events: participants will remain in the FAS and SS and their observed outcomes will be included in the primary treatment-policy analysis, whereas they will be excluded from the PPS. Glucocorticoid dose stability (stable vs. unstable according to the predefined criteria) will be included as a binary covariate in a prespecified sensitivity analysis, rather than in the primary model.

For the three key secondary endpoints (change from baseline to post-treatment in ISI score, PSG-derived sleep efficiency, and PSG-derived TST), the Benjamini-Hochberg procedure will control the false discovery rate at 5%. The remaining exploratory outcomes will be reported with nominal *p*-values without adjustment and interpreted as hypothesis-generating.

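### Unauthorised hypnotic users meet a withdrawal criterion during treatment yet are promised a place in the FAS; if withdrawal ends assessment, they have no post-baseline PSQI to analyse

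*Protocol article*

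**What the plan says.** Section 2.2.3 (Withdrawal criteria) has seven items. Item (7) is "Those who take sedative-hypnotic drugs without authorization in the course of treatment". Items (4) to (6) are "Patients whose disease progressed during the course of the study, making them unsuitable for continuation", "Patients who did not comply with the subject research process after entering the study" and "Those who were difficult to assess due to poor adherence to and noncompliance with medical advice during the course of treatment". Items (1) to (3) cover loss to contact, refusal to continue treatment, and discontinuation because of adverse events. The section does not say whether withdrawal is from treatment or from the trial, or whether anyone withdrawn is still assessed.

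Section 2.6.1 (Data sets definition) says: "Cases with unauthorized use of sedative-hypnotic medications will be excluded from the PPS but retained in the FAS and SS analyses". It defines the FAS as "All randomized participants who received at least one intervention and had at least one post-baseline efficacy assessment".

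Section 2.2 says unauthorised hypnotic use will be recorded and dealt with in per-protocol and sensitivity analyses.

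Section 2.6.2 fits the primary MMRM to post-baseline PSQI scores only, with baseline as a covariate, under missing at random. Its intercurrent-event statement reads "Major changes in glucocorticoid exposure will be treated as intercurrent events"; hypnotic use is not named there.

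Section 2.7 places the first post-baseline data collection on the final treatment day, and Table 2 shows it at week 4.

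**The concern.** One section removes hypnotic users during treatment. Another counts on them in an analysis set whose entry condition is first met, for every efficacy outcome listed in section 2.4, at the end of treatment. Unless withdrawn participants are still assessed, the retention promise has no data behind it.

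A participant who reaches for a hypnotic in an insomnia trial is probably sleeping badly, and this may happen more often in one arm. Removing such people before their first outcome visit makes missingness depend on the outcome the trial is meant to measure. The comparison then drifts towards an effect among those who did not need a hypnotic. The trial's own rule would create these gaps, and the data could have been collected.

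Items (2) to (6) cause the same avoidable loss for people who refuse or stop treatment, progress, or adhere poorly, although section 2.6.1 does not promise FAS retention to them by name.

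**Working it through.** The plan gives no figure on this point, so the check sets the sections side by side.

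1. **Trigger.** Unauthorised hypnotic use during treatment meets item (7) of section 2.2.3. The treatment phase is weeks 1 to 4 (Table 2).

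2. **First outcome.** Table 2 has no PSQI, ISI, PSG, actigraphy, 5-HT, BAI, BDI, FSS or ESS between baseline and week 4. Section 2.7 puts the post-treatment assessment on the final treatment day.

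3. **FAS entry.** Section 2.6.1 asks for an efficacy assessment after baseline. From step 2, someone who leaves assessment before the final treatment day has none of the outcomes listed in section 2.4. Table 2 does show a sleep diary in weeks 1 to 3. Section 2.4 does not list it as an efficacy outcome, however, and section 2.7 describes diaries only for the assessment phases. Even if a diary counted for FAS entry, it supplies no PSQI value.

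4. **Primary model.** The MMRM's dependent values are the PSQI scores at post-treatment, 1 week and 1 month. A participant with none of the three contributes nothing to the estimate.

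5. **Sensitivity analyses.** Section 2.6 bases the analyses on the FAS and PPS. Item (7) cases are out of the PPS by rule, and from step 3 would normally be outside the FAS. Multiple imputation and the delta-adjusted analysis, if run on the FAS, would not include them.

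6. **What withdrawal means.** Items (2) and (3) take stopping treatment as the trigger, so withdrawal reads as something further. Item (1) also applies in the follow-up phase, when no treatment is left to stop. Item (5) concerns the research process. All share one list with loss to contact, and none keeps assessments. The natural reading is leaving the trial, but the section does not say so.

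7. **Illustration of size, with assumed rates.** Let p be the share withdrawn in each arm, and let those withdrawn score g PSQI points worse than those who stay. Then each full-arm mean equals the stayers' mean + p × g, so

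   stayers' contrast (sham − acupuncture) = full contrast − (p_sham − p_acu) × g.

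| p_acu | p_sham | g | Shift in points | Share of planned 2.70 |
|---|---|---|---|---|
| 0.05 | 0.15 | 2 | 0.10 × 2 = 0.20 | 0.20/2.70 = 7% |
| 0.08 | 0.20 | 3 | 0.12 × 3 = 0.36 | 0.36/2.70 = 13% |
| 0.10 | 0.30 | 4 | 0.20 × 4 = 0.80 | 0.80/2.70 = 30% |

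Only the 2.70 comes from the protocol (section 2.2.4); every p and g is assumed. With more sham withdrawals, as tabulated, the stayers' contrast understates the full contrast. With the imbalance reversed it overstates it by the same amount, and with equal shares and equal g the shift is zero. These are raw means; adjustment for baseline PSQI may reduce the shift.

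**The case against.** The strongest reply is that section 2.2.3 never says withdrawal is from the study. If it means stopping study treatment with assessments continued, sections 2.2.3 and 2.6.1 are compatible. Three things favour that reading: the explicit FAS retention of hypnotic users, the plan in section 2.2 to address their use in sensitivity analyses, and the PPS requirement of at least 80% of sessions, which implies that less adherent participants can be in the FAS. This stands in part. A reader might infer that the two rules cannot both be carried out. The documents do not support that, because everything depends on what withdrawal ends, and that is unstated.

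A reader might also infer that withdrawing hypnotic users, non-adherers and progressors contradicts a promised treatment-policy analysis. It does not. The words "their observed outcomes will be included in the primary treatment-policy analysis" refer to participants with major glucocorticoid changes, which are not a withdrawal criterion. The only overlap is indirect: if disease progression under item (4) comes with such a change, withdrawal from assessment would leave no outcomes to include.

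A third reply is that a condensed article may leave follow-up after withdrawal to the full protocol. That would answer a complaint about silence alone. Here two printed rules pull against each other, and the article's own visit schedule makes the tension bite.

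Finally, the assumed case in the working table biases against acupuncture, so it shows no false-positive risk. That is correct for that case; the opposite imbalance is equally undocumented and cannot be ruled out.

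**Conclusion.** The point holds for item (7): withdrawal for hypnotic use during treatment and the promised FAS retention need reconciling. If withdrawal ends assessment, which is the more natural reading, those withdrawn before the final treatment day supply nothing to the primary MMRM and would normally be outside the FAS and any FAS-based sensitivity analysis. If it ends only treatment, the defect is an ambiguity about who supplies primary-outcome data, and the same sentence cures it.

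The loss strains the missing-at-random assumption; the documents do not show that the assumption is violated. Neither size nor direction can be derived from them, since they give no rate of hypnotic use and no outcome difference. Items (2) to (6) raise the same avoidable data loss, without a direct contradiction.

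**What to change.** Reconcile sections 2.2, 2.2.3, 2.6.1 and 2.6.2:

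- State in section 2.2.3 that criteria (2) to (7) concern the end of study treatment and do not end data collection.
- Add that participants meeting them who still consent to follow-up complete the scheduled post-treatment, 1-week and 1-month PSQI and ISI, remotely if needed, and that these data enter the FAS analysis.
- Name in section 2.6.2 how unauthorised hypnotic use is handled as an intercurrent event, consistently with the FAS retention already promised and with the sensitivity analyses mentioned in section 2.2.

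This concerns outcome collection only. Whether treatment continues remains a decision for the investigators.

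The cost is a short amendment and modest follow-up effort; section 2.4.2.2 itself describes the PSQI and ISI as easy to give remotely. It is best done now: the Trial status section reports that recruitment is ongoing, with completion expected by 20 December 2026, and a PSQI not taken at its visit cannot be recovered later.
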